### Concomitant illnesses

Additional illnesses present at entry to the study are regarded as con­comitant illnesses and will be documented on the case record form pro­vided.

Any concomitant disorder such as diabetes, hypertension, heart failure etc. should be controlled before entry into the study by appropriate medication which should, if possible, not be changed during the entire study period.

Patients with congestive heart failure stadium III of IV according to the NYHA classification will be excluded from the study.

Concomitant disorders, current medication and any changes in concomitant disorders and/or methotrexate, NSAID or prednison dosage have to be documented appropriately in the case record forms.

Illnesses occurring during the study period are to be regarded as adverse events and will each be documented in the medical records. Adverse events will be documented on a separate "Adverse event" page in the case record form. Especially infections, malignancies and hospitalisation will be noted on a separate page in the case record form.

Application of study medication may be continued during intercurrent illnesses - if clinically justifiable and as long as none of the withdrawal criteria is met.

### Concomitant treatment

All treatments being taken by the patients on entry to the study and all treatments given in addition to the study treatment during the study are regarded as concomitant treatments and must be docu­­mented on the case record form.

### Concomitant medications

Should be kept to a minimum during the study. However, if these are considered necessary for the pa­tient's welfare and will not interfere with the study medication, they may be given at the discretion of the investigator. If the patient is responding to adalimumab treatment, tapering of the prednisone is allowed after week 16.

The following concomitant treatments (for RA) are permitted during this study, provided that the patients have received a stable dose for at least 28 days before entering the study:

- nonsteroidal anti-inflammatory drugs (NSAIDs) including acetylsalicylic acid
- oral steroids, if not exceeding a prednisone equivalent of 10 mg daily (stable for 2 months prior to entry)
- methotrexate (5-30 mg/week, obligated in all patients)

The following concomitant treatments are not permitted during this study (see exclusion criteria):

- intra-articular corticosteroid injections
- oral steroids, if exceeding a prednisone equivalent of 10 mg daily
- DMARDs other than methotrexate
- any alkylating agents (e.g. cyclophosphamide, chlorambucil)
- any anti-metabolites
- any other monoclonal antibodies, growth factors, or cytokines
- any experimental drug

It is important that steroid treatment be kept to a minimum. Changes of NSAIDs and methotrexate should be avoided. Decreases in steroid therapy (drug or dosing) are allowed after evaluation of response at 16 weeks. If there is a clear reason to do so, the reason and the changes have to be documented in the case record form.

If the administration, a change in dosing or the stopping of any concomitant treatment is necessary, it must be reported in the patient's medical records and the case record form. As far as possible, no changes should be made to the concomitant treatment during the study.

Patients undergoing surgical procedures involving general anesthesia may interrupt study medication. In total, a single dosing interruption up to 10 days is allowed (see also *Withdrawl and replacement of patients*).

Patients requiring surgical procedures involving local or regional anesthesia may continue with study medication.

Infections

Serious and opportunistic infections have been described in patients receiving TNF blocking agents, but it is not clear that their incidence is higher than in patients with rheumatoid arthritis using other forms of DMARD therapy and/or corticosteroids. TNF blocking agents should not be started or should be discontinued when serious infections occur, including septic arthritis, infected prostheses, acute abscess, osteomyelitis, sepsis, systemic fungal infections, Listeria etc. Treatment with TNF-blockers in such patients should only be resumed if the infections have been treated adequately.

Pregnancy

An embryo-fetal perinatal developmental toxicity study has been performed in monkeys and has revealed no evidence of harm to the fetuses due to adalimumab, however no adequate and well-controlled studies in pregnant women have been performed. For this reason pregnancy is an exclusion criterium in this study.

Overdosage

The maximum tolerated dosage of adalimumab has not been established in humans. Multiple doses up to 10mg/kg have been administered to patients in clinical trials without evidense of dose-limiting toxicities. In case of an overdosage, the patient will be monitored for any signs or symptoms of adverse reactions or effects and treated when necessary.

Adverse events

An adverse event is any event which impairs the wellbeing of the patient during the period of observation in a clinical study, including intercur­rent illness or accident. The term ad­verse event does not imply a causal re­lation­ship with the study treat­ment.

The period of observation for adverse events extends from the time the patient gives informed consent until he or she undergoes a final exami­nation as part of the study, including periods before and after an active treatment phase during which no drug or other treatment is given. The period may also include a specified number of days after the final ex­amination during which time serious adverse events must be re­ported (see below). Adverse events occurring after the end of the study must be re­ported if the investigator considers there is a causal relationship with the study medica­tion.

All patients experiencing adverse events ‑ whether considered as­soci­ated[[1]](#footnote-2) with the use of the study medication or not ‑ must be monitored until symptoms subside and any abnormal laboratory values have re­turned to baseline, or until there is a satis­factory explanation for the changes ob­served, or until death, in which case a full pathologist's re­port should be supplied, if possible. All findings must be reported in the patient's medi­cal re­cords.

All drug-related adverse events, including intercurrent illnesses, must be reported on and docu­mented as described below.

Adverse events are divided into the categories "serious" and "non­seri­ous". This determines the procedure that must be used to re­port/document the adverse event (see below).

*Definition of serious and non-serious adverse events*

A serious adverse event is any adverse event occurring at any dose that results in:

1. Death
2. A life-threatening event
3. Inpatient hospitalization or prolongation of existing hospitalization
4. Persistent or significant disability/incapacity
5. Congenital anomaly/birth defect

Adverse events that do not fall into these categories are defined as non-serious.

*Reporting/documentation of adverse events*

*Serious adverse events*

All serious adverse events which occur during the period of observation, whether consid­ered to be associated with the study medication or not must also be docu­mented in the case record form.

Where necessary, inves­tigators will in­form the medical ethics committee and authorities.

*Non-serious adverse events*

These are to be documented in the case re­cord form if related with the study medication.

*Adverse events occurring after the period of observation*

Any adverse event occurring at any time after the end of the study and considered to be caused by the study medication - and therefore a possible adverse drug reac­tion - must be re­ported as above.

*Assessment of severity*

Regardless of the classification of an adverse event as serious or non-se­ri­ous (see above), its severity must be assessed as mild, moderate or se­vere, according to medical criteria alone:

mild = does not interfere with routine activities

moderate = interferes with routine activities

severe = impossible to perform routine activities

It should be noted that a severe adverse event need not be serious in nature and that a serious adverse event need not, by definition, be se­vere. Regardless of se­verity, all serious adverse events must be re­ported as above.

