### Exclusion criteria:

1. Pregnancy
2. Breastfeeding
3. A history of or current acute inflammatory joint disease of different origin e.g. mixed connective tissue disease, seronegative spondylarthropathy, psoriatic arthritis, Reiter’s syndrome, systemic lupus erythematosus or any arthritis with onset prior to age 16 years
4. Acute major trauma

5) Therapy within the *previous 60 days* with:

- any experimental drug
- alkylating agents, e.g. cyclophosphamide, chlorambucil
- antimetabolites
- monoclonal antibodies (including infliximab and etanercept)
- growth factors
- other cytokines

6) Therapy within the *previous 28 days* with:

- parenteral or intraarticular corticoid injections
- oral corticosteroid therapy exceeding a prednisone equivalent of 10 mg daily
- present use of DMARDs other than methotrexate

7) Receipt of any live (attenuated) vaccines within 4 weeks prior to baseline

8) Fever (orally measured > 38 °C), chronic infections or infections requiring anti-

microbial therapy

9) Known positive reaction to hepatitis B surface antigen or Hepatitis C antigen

10) Other active medical conditions such as inflammatory bowel disease, bleeding

diathesis, or severe unstable diabetes mellitus

11) Manifest cardiac failure (stage III or IV according to NYHA classification)

12) Progressive fatal disease/terminal illness

13) A congenital or acquired (known HIV-positive status) immunodeficiency

1. 14) a history of lymphoproliferative disease or treatment with total lymphoid

irradiation.

15) A white cell count less than 3.5 x 109/l

16) Platelet count less than 100 x 109/l

17) Haemoglobin of less than 5.3 mmol/l

18) Body weight of less than 45 kg

19) History of drug or alcohol abuse

20) Any concomitant medical condition which would in the investigator’s opinion compromise the patient’s ability to tolerate, absorb, metabolize or excrete the study medication.

21) Inability to give informed consent

22) Mental condition rendering the patient unable to understand the na­ture, scope

and possible consequences of the study and/or evidence of an uncooperative attitude.

Screenings procedures

Screening will be done within 1-2 weeks before baseline to assess the in- and exclusion criteria and to evaluate if all the safety parameters are met. All patients sign their informed consent form before baseline.

Variables and schedule of observations

The following will be determined in accordance with the "Schedule of observations" *(see page 2-3*).

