### Primary endpoint

The primary endpoint of the study is the percentage of patients with a moderate to good response to adalimumab treatment at 16 weeks according to the Eular response criteria which is also applied in routine rheumatological practice.

A decrease in the DAS 28 value must be ≥ 1.2 at any given timepoint after initiation of treatment for continuation of reimbursement by the insurance company.

| **DAS 28 score at**  **(week 16)** | **Improvement in DAS 28 at week 16 compared to baseline (week 0)** | | |
| --- | --- | --- | --- |
|  | **>1.2** | **> 0.6 en  1.2** | ** 0.6** |
| ** 3.2** | **Good** |  |  |
| **> 3.2**  **and  5.1** |  | **Moderate** |  |
| **> 5.1** |  |  | **None** |

*Tabel 1: Eular response criteria*

Furthermore the primary endpoint of the study is to search for clinical parameters and/or serological markers that possibly distinguish responders from non-responders to TNF-α blockade by adalimumab.

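### The in-study prohibited list omits the parenteral corticosteroids named in exclusion criterion 6, and the uncontrolled week-16 response does not separate out DAS 28 falls helped by added steroid or methotrexate

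*Protocol*

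**What the plan says.** **Before entry.** Exclusion criterion 6 rules out patients who, within the previous 28 days, had "parenteral or intraarticular corticoid injections" or oral steroid above 10 mg prednisone equivalent daily, and patients using a DMARD other than methotrexate.

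**During the study.** The prohibited list in Concomitant medications is introduced by "The following concomitant treatments are not permitted during this study (see exclusion criteria". Its steroid entries are "intra-articular corticosteroid injections" and "oral steroids, if exceeding a prednisone equivalent of 10 mg daily". The permitted list has "oral steroids, if not exceeding a prednisone equivalent of 10 mg daily (stable for 2 months prior to entry" and "methotrexate (5-30 mg/week, obligated in all patients".

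**On changes.** The same section asks for minimal steroid use and says "Changes of NSAIDs and methotrexate should be avoided". It allows steroid decreases once response has been assessed at week 16, and it wants concomitant treatment left unchanged where possible. A necessary change must be recorded in the medical records and the case record form. Other concomitant medication judged necessary, and not interfering with study drug, is left to the investigator's discretion.

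**Endpoint.** "The primary endpoint of the study is the percentage of patients with a moderate to good response to adalimumab treatment at 16 weeks", by the EULAR criteria. Table 1 classifies on the DAS 28 reached and its improvement from baseline. The Primary endpoint section adds a search for factors that separate responders from non-responders, and Data analysis plans logistic regression for predictors of response. Design states that there is no control group.

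**The concern.** Criterion 6 treats a parenteral steroid in the 28 days before entry as disqualifying. The in-study list cites the exclusion criteria and repeats most of the therapies in criteria 5 and 6 one by one, yet parenteral steroid is not among them. An investigator cannot tell from the text whether an intramuscular or intravenous steroid shortly before the week-16 visit is prohibited. Separately, a prednisone or methotrexate increase within the stated ranges goes against the protocol's advice but breaks no prohibition.

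Either change could lower the week-16 DAS 28. Without a control group nothing offsets that effect, and the endpoint sets no condition on background treatment. Added treatment would most plausibly go to patients doing poorly, so the error would favour response, and a larger sample would not shrink it. The same classification feeds the marker comparison, where a patient moved by steroid would sit among the adalimumab responders.

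**Working it through.** The protocol gives no figure that depends on this point, so the check is a comparison of text followed by an illustration of size.

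**Text comparison**

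| Treatment | Before entry | Week 0 to 16 |
|---|---|---|
| Parenteral steroid | Excluded (28 days) | On neither the prohibited nor the permitted list |
| Intra-articular steroid | Excluded (28 days) | Prohibited |
| Oral steroid above 10 mg/day | Excluded (28 days) | Prohibited |
| Oral steroid up to 10 mg/day | Allowed if stable for 2 months | Permitted on that condition; an increase is discouraged, not prohibited |
| Methotrexate 5-30 mg/week | Required, stable for 28 days | Required; changes are discouraged, not prohibited |
| Other DMARDs | Excluded | Prohibited |

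The mismatch between the two lists is in the first row. The classification problem arises in the first, fourth and fifth rows.

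**Classification rule used.** Table 1 is read as: responder if improvement exceeds 1.2, or if it exceeds 0.6 and the week-16 DAS 28 is at most 5.1. Some signs and merged cells are lost in the extracted table, so this reading is an assumption.

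**Assumed inputs (none is in the protocol).** Baseline DAS 28 is N(5.5, 1.1). The fall on adalimumab is N(1.5, 1.2), independent of baseline. Added treatment lowers week-16 DAS 28 by a further 0.3, 0.6 or 0.9.

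**Simulated result.** About 72% respond. Non-responders are about 28%, or 0.28 × 120 ≈ 34 patients. About 37% of them have a week-16 DAS 28 above baseline. Applying the baseline limit of 3.2 leaves the conversion rates essentially unchanged.

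| Extra fall | All non-responders converted | Those worsened above baseline | The remaining 63% |
|---|---|---|---|
| 0.3 | 27% | 0% | 27/0.63 ≈ 43% |
| 0.6 | 49% | 0% | 49/0.63 ≈ 78% |
| 0.9 | 66% | 23% | (66 − 0.37 × 23)/0.63 ≈ 91% |

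The zeros need no simulation. A patient whose own fall is below 0 and who gains at most 0.6 has a total fall below 0.6, and Table 1 requires more than 0.6.

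**Effect on the percentage.** Inflation = (share of all patients who are escalated non-responders) × (share of those converted). Using the all-non-responder rates:

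- Low: 0.05 × 0.27 = 1.35 points; 120 × 0.0135 = 1.6 patients.
- Middle: 0.10 × 0.49 = 4.9 points; 5.9 patients.
- High: 0.15 × 0.66 = 9.9 points; 11.9 patients.
- If all those escalated had worsened above baseline and the effect is 0.6 or less: 0 points.

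**How demanding those shares are.** Of about 34 non-responders, 5%, 10% and 15% of the 120 are 6, 12 and 18 patients. That is 6/34 ≈ 18%, 12/34 ≈ 35% and 18/34 ≈ 53% of all non-responders.

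**Yardstick.** The 95% half-width is 1.96 × √(p(1 − p)/120): 8.9 points at p = 0.5, 8.2 at 0.7 and 7.2 at 0.8.

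**The case against.** The strongest reply is that the protocol already leans against these changes. It asks for minimal steroid use, names only steroid decreases as allowed and only after week 16, and wants no changes where possible. It permits oral steroid on condition of stability before entry, which a new start would not meet. The prohibited list's reference to the exclusion criteria can be read as carrying the parenteral exclusion over, which makes a drafting slip at least as likely as an intended gap. All of this stands. A reader might infer that the protocol freely allows steroid or methotrexate increases before week 16. It does not: they are discouraged and documented. What remains is that they are not prohibited and that the two lists differ on parenteral steroid.

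A reader might also take the middle figure, about 5 points, as the expected bias. The documents do not support that. It needs about 35% of all non-responders to receive treatment the protocol discourages, and it averages over patients just short of the cut-off. If the treated patients are those who have worsened above baseline, conversion is zero for an added effect up to 0.6.

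Finally, handling of background-treatment changes may sit in a statistical analysis plan that is not shown, and the changes are recorded, so a rule could be applied later. The study is also exploratory, with no stated success threshold for a few points to overturn. This is a good reason not to insist that the primary definition itself be changed. It does not remove the mismatch between the two lists.

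**Conclusion.** The point holds in limited form. Exclusion criterion 6 and the in-study prohibited list disagree on parenteral corticosteroid and must be reconciled. Prednisone increases up to 10 mg daily and methotrexate increases within 5-30 mg/week before week 16 are discouraged and documented but not prohibited. The endpoint as written credits any resulting DAS 28 fall to adalimumab, in both the response percentage and the responder/non-responder comparison.

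The size cannot be fixed from the protocol. On the assumed distributions and escalation rates it runs from about zero to several percentage points. The upper end, near 10 points and comparable to the sampling error at 120 patients, requires more than half of all non-responders to be escalated and should not be taken as likely.

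A reader might conclude that the primary endpoint has to be redefined so that escalation is non-response. That is a choice of estimand which the documents neither require nor rule out, so such a classification belongs beside the as-observed EULAR result rather than in its place.

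**What to change.** 1. Reconcile exclusion criterion 6 and the prohibited list in Concomitant medications on parenteral corticosteroid, so that both state the same intention. Which intention is clinically right is for the investigators.

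2. Keep the as-observed EULAR week-16 percentage and marker comparison. Beside them, pre-specify an analysis that counts as a non-responder any patient with one of the following documented between week 0 and week 16: a parenteral or intra-articular corticosteroid, a prednisone start or increase, a methotrexate increase, or a new DMARD. Report the number of such patients. If added treatment can only lower DAS 28, the two percentages bracket the response that would have been seen without it. This is an analysis label only and leaves the EULAR criterion that governs continuation of treatment untouched.

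**Cost.** Protocol wording and one extra analysis. The data are already to be recorded under Background information, Concomitant illnesses, Concomitant treatment and Concomitant medications. The second percentage may be slightly lower. A true responder given steroid for a reason other than RA would be counted as a non-responder in that analysis, which blurs the marker comparison in the opposite direction and is another reason to show both.

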## **Safety Variables**

### Adverse events

Adverse events observed by the investigator or reported by the patient will be documented as described below in this study protocol. Infections, malignancies and hospitalisation during adalimumab will be noted on a separate page in the case record form.

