## **Clinical variables**

As clinical safety monitoring the following examinations will be performed:

A complete medical history will be taken before enrollment. Interest will be focused on current concomitant diseases and DMARD-history.

Physical examination will be performed at screening. Vital signs (blood pressure, pulse frequency, body weight, oral body temperature) will be determined at each visit.

Any evaluations that are abnormal and considered to be related to the study medication will be followed until they return to baseline or are judged not to be clinically significant.

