# 3. Methods of investigation

Clinical examinations

The clinical examinations including vital signs as well as safety assessments will be performed as usual in routine clinical practice. Blood will be drawn at the 7 visits 1 EDTA tube, 1 lithium heparine tube, 2 serum tubes and a 2.5 ml tube mRNA for storage at each time point. Serum will be immediately frozen at -70°C. The material will be used for detection of acute phase reactants, biologic markers (such as cytokines), anti-antibodies, leukocyte differential, and gene activation (micro array) in relation to the disease.

All samples must be clearly *labeled* (using labeling that can withstand freezing in liquid nitrogen/dry ice) including patient number and date and time of sampling.

Routine bloodtests for haematology and chemistry will be performed each visit including ESR and CRP as measures of disease activity. Routine urine samples are taken to check for proteinuria, blood and leucocyten and dipstick testing.

At baseline, after 28 and 52 weeks immunological assays e.g. anti-ds DNA (Crithidia), IgM rheumatoid factor, ANA and anti-CCP will be performed. This will be 1 serum tube at 3 visits.

Genetic polymorphisms

Only at baseline 1 additional EDTA tube will be drawn for DNA isolation and study of genetic markers, e.g. genetic polymorphisms in the TNF- alpha genes that may pedict efficacy and side-effects of treatment.

Bonemetabolism

Urine samples will be frozen from 6 visits for analysis of markers involved in bone resorption e.g. CTX I and CTX II for cartilage degradation.

Other markers for bone formation e.g. osteocalcin will be determined in the serum.

Bonemineraldensity

A DEXA scan will be performed at baseline and at 52 weeks to compare bonemineraldensity changes after adalimumab treatment.

Radiologic progression

X-rays of hands and feet will be performed at baseline and 52 weeks to evaluate disease progression using the modified Sharp v.d. Heijde scoring method.

Disease activity

This will be assessed by the DAS 28, the RADAI, HAQ questionnaires, the SF 36 (short health survey), response criteria number of clinical tests. Furthermore diverse analogue scales will be used to asses disease severity and pain in order to calculate the ACR response criteria.

Employment

At baseline, 28 weeks and 52 weeks questionnaires will be used to assess if adalimumab treatment has any influence on employment status, sickleave and workingcapacity (e.g.100 % fulltime or 50% parttime).

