**Footnote**: **Note of clarification on paragraph 29 of the WMA Declaration of Helsinki**

The WMA hereby reaffirms its position that extreme care must be taken in making use of a placebo-controlled trial and that in general this methodology should only be used in the absence of existing proven therapy. However, a placebo-controlled trial may be ethically acceptable, even if proven therapy is available, under the following circumstances:

  - Where for compelling and scientifically sound methodological reasons its use is necessary to determine the efficacy or safety of a prophylactic, diagnostic or therapeutic method; or

  - Where a prophylactic, diagnostic or therapeutic method is being investigated for a minor condition and the patients who receive placebo will not be subject to any additional risk of serious or irreversible harm.

All other provisions of the Declaration of Helsinki must be adhered to, especially the need for appropriate ethical and scientific review.

The Declaration of Helsinki (Document 17.C) is an official policy document of the World Medical Association, the global representative body for physicians. It was first adopted in 1964 (Helsinki, Finland) and revised in 1975 (Tokyo, Japan), 1983 (Venice, Italy), 1989 (Hong Kong), 1996 (Somerset-West, South Africa) and 2000 (Edinburgh, Scotland). Note of clarification on Paragraph 29 added by the WMA General Assembly, Washington 2002.

1. "Associated" means a reasonable possibility that the event may have been caused by the drug. If the [↑](#footnote-ref-2)

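### The protocol gives two different rules for entering non-serious adverse events in the case record form, and one of them leaves out events judged unrelated to adalimumab

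*Protocol*

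**What the plan says.** All places are in section 2 of the protocol unless stated otherwise.

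- **Definition (Adverse events).** "An adverse event is any event which impairs the wellbeing of the patient during the period of observation in a clinical study". The sentence goes on to include intercurrent illness and accident, and the next one says that the term implies no causal link with treatment.
- **First recording rule (Concomitant illnesses).** "Illnesses occurring during the study period are to be regarded as adverse events", each noted in the medical records. Then: "Adverse events will be documented on a separate 'Adverse event' page in the case record form". No condition on relatedness or seriousness is attached.
- **Second recording rule (Reporting/documentation of adverse events).** Serious events go into the case record form whether or not they are thought to be associated with adalimumab. Non-serious events go into the case record "form if related with the study medication".
- **Special categories (Safety Variables, Adverse events).** "Infections, malignancies and hospitalisation during adalimumab will be noted on a separate page in the case record form". This too has no relatedness condition.
- **Follow-up of abnormal findings (Clinical variables).** "Any evaluations that are abnormal and considered to be related to the study medication will be followed until they return to baseline", or until they are judged not clinically significant. By contrast, the Adverse events section requires monitoring of every patient with an adverse event, associated or not.

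**The concern.** For a non-serious event judged unrelated to adalimumab, the two recording rules prescribe different contents of the case record form. Staff following Concomitant illnesses would complete an adverse-event page. Staff following Reporting/documentation of adverse events would not.

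Non-serious is not the same as trivial here. Seriousness turns on death, threat to life, hospitalisation, disability or congenital anomaly, and the protocol itself notes that a severe event need not be serious. An episode that makes routine activities impossible but needs no admission can fall in the disputed group.

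Under the second rule, the investigator's attribution decides whether the event reaches the study data at all. That attribution is hard to verify. The Design section provides no control group, and methotrexate is compulsory for all patients (Concomitant medications), so a second plausible cause is always present. If only related events are entered, attribution cannot be revisited from the case record forms. If all are entered with relatedness as an item, it can. Side-effects are also among the outcomes that the genetic-marker question hopes to predict (Objectives, research question 4), so how completely they are recorded matters beyond the safety listing.

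**Working it through.** The plan states no figure on this point and no calculation applies. The check is to take each kind of event through both rules.

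| Event | Concomitant illnesses | Reporting/documentation of adverse events | Agreement |
|---|---|---|---|
| Serious, related or not | Entered | Entered | Yes |
| Non-serious, related | Entered | Entered | Yes |
| Non-serious infection or malignancy, unrelated | Entered, with its own page | Not entered by this rule, but the separate page still applies | Captured either way |
| Any other non-serious event, unrelated | Entered | Not entered | **No** |

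Hospitalisation makes an event serious and also has its own page, so it is captured on both counts. The conflict is confined to the last row.

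**Does other text settle which rule governs?** Safety Variables says that events are documented in the manner set out further on. Both rules stand further on, so this does not rank them. The Adverse events section adds that drug-related events, intercurrent illnesses included, must be reported. That leans towards the second rule but does not withdraw the first.

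**What trace is left under the second rule?** Events remain in the medical records. Treatments given during the study are entered in the case record form (Concomitant treatment), as are changes in concomitant disorders (Concomitant illnesses). A treated event might thus show up as a medication entry with no matching adverse event.

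**Follow-up of abnormal values.** Clinical variables makes follow-up depend on relatedness. The Adverse events section does not, but it applies only to patients with an adverse event. The two rules therefore treat an unrelated abnormal value differently, depending on whether the patient counts as having an adverse event.

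**Number affected.** The protocol plans 120 patients but gives no rate of adverse events and no share judged unrelated, so no estimate is offered.

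**The case against.** The strongest defence is that the rules fit together: Concomitant illnesses says where events are written down, and Reporting/documentation of adverse events says which ones. The second section is the more specific. It says that seriousness determines the procedure, and it deliberately contrasts serious events, entered regardless of association, with non-serious ones. In an exploratory study of an approved, prescribed drug in routine practice, collecting only related non-serious events may be a reasonable choice. Unrelated events also stay in the medical records, so a single centre can look them up.

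Part of this stands. The source record softens the harm, and a reader might wrongly infer that unrelated events are lost altogether; they are not. But the protocol never says that the second rule overrides the first, and the first names the case record form page without any limit. A record kept at source is also not in the study data.

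A reader might also infer that a symptom-free laboratory abnormality blamed on methotrexate falls outside the definition and outside every follow-up rule. The documents do not support that as a firm conclusion:

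- Intercurrent illness is inside the definition. Impaired wellbeing can be read to cover a clinically significant silent finding: adverse-event monitoring names abnormal laboratory values, and the mild grade covers events that do not disturb routine activities.
- Adverse-event monitoring may stop once the change is satisfactorily explained, and methotrexate could be that explanation. Widening the definition might add no follow-up.
- "Routine bloodtests for haematology and chemistry will be performed each visit" (section 3, Clinical examinations), so an abnormal value would usually be seen again. This is a schedule, not a follow-up rule: the gap between visits reaches 16 − 4 = 12 weeks, and no further assessments follow for non-responders stopped at week 16.
- Counting combinations of attribution and other adverse events that lack a rule would measure no risk.

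The footnote on association, which "means a reasonable possibility that the event may have been caused by the drug", breaks off in the available text. Whether its threshold also governs relatedness cannot be judged, and nothing here rests on it.

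**Conclusion.** The recording conflict is real. It is confined to non-serious events judged unrelated, outside the infections, malignancies and hospitalisations that have their own page. For these events, the content of the safety data depends on which section is followed and, under the second, on an attribution that is hard to verify. The conclusion rests on reading the sentence in Concomitant illnesses as written, without an implied relatedness limit.

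The laboratory follow-up wording deserves only a minor clarification. The primary endpoint is EULAR response at week 16 and is unaffected. This is a low-priority fix to safety recording.

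**What to change.** 1. In Reporting/documentation of adverse events, require all non-serious adverse events to be entered in the case record form whatever their relatedness, in line with Concomitant illnesses, and record relatedness as a separate item. Bring the nearby sentence on reporting drug-related events into line.
2. As a minor companion change, remove the relatedness condition from the follow-up sentence in Clinical variables. Keep its provision that follow-up may end once a finding is judged not clinically significant, so that trivial values add little work.

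The cost is a wording change in two places, more adverse-event pages, some extra follow-up of abnormal values and a somewhat higher reported event rate. No scheduled visit or test is added.
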